### Sample Size Calculation

We propose recruiting 400 participants for each group (N=1200) at baseline. Imamura and colleagues assessed the effectiveness of integrative CBT (iCBT) in reducing the risk of MDE in a RCT [30]. Participants (N=762) were randomized into control and intervention group. Over 12 months, 0.8% and 3.9% of participants in the intervention and control group developed MDE, respectively. Based on these proportions, 374 participants in each arm are needed to detect the difference at a power of 0.80 and alpha level of.05. The sample size was calculated using statistical software STATA 14.0 (syntax: power two proportions 0.008 0.039) [31]. This is consistent with the average number of participants in the previous RCTs [32]. To offset attrition, we plan to provide a Can $20 incentive for participating in an assessment in appreciation of the participants’ time and efforts.

## Results

This study was approved by the Conjoint Health Research Ethics Review Board of the University of Calgary (Ethics ID: REB14-2365). The trial is funded by a team grant from the Movember Foundation, a global charity for men’s health. BroHealth was developed at Digital Emergency Medicine, University of British Columbia, and the usability testing is complete. It is anticipated that the RCT will be completed by 2018.

## Discussion

### Principal Findings

BroHealth is novel in several ways. First, BroHealth focuses on early prevention of major depression, rather than providing treatment to those who already have MDE. The outcomes include not only reduced risk of MDE, but also improved work functioning, productivity, and return on investment. Second, BroHealth was developed through a gender lens, focusing on the working men who are at high risk of having MDE. Third, the development of BroHealth was informed by men’s preferences of design features of e-mental health programs, through a national survey of the target population. To this extent, this approach enhances the acceptability of BroHealth by working men who are at high risk of MDE.

### Limitations

BroHealth was designed to be used by male workers who have access to the Internet. Men who don’t have Internet access for personal use will not be included. Some elements of BroHealth were based upon existing programs. For example, the CBT program of BroHealth was adapted from the abbreviated version of the UK Living Life to the Full (LLTTF), and the mindfulness relaxation program was developed by University Health Network in Ontario. However, the French materials for the mindfulness relaxation program were not available. This may affect the effectiveness of BroHealth in French speaking participants. We will examine this potential impact by conducting the proposed analyses in English and French speaking participants separately. The incidence of MDE will be measured by CIDI-SF for MDE, which is a fully structured diagnostic interview, rather than by physician diagnosis. Therefore, misclassification of diagnosis is possible.

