### Statistical Analysis

All data analyses will be conducted using the most recent version of STATA. An Intention-to-treat (ITT) principle will be used in the analysis (eg, initial intervention assignment rather than intervention received will be used in the analysis).

For the primary objective, the proportions of MDE over 12 months will be estimated for each group and will be compared using chi-square tests between control versus intervention #1, and control versus intervention #2. Logistic regression modeling will be used to examine the effect of the intervention on the outcome, controlling for the effects of baseline confounders. Contrast analysis will be conducted to compare different intervention groups (intervention #1 vs intervention #2) as one of the secondary objectives.

For the secondary objectives, the distributions of the changes in the depression and anxiety scores at 6 and 12 months in the intervention and control groups will be examined. The means of the changes between the intervention and control groups will be compared using *t* tests.

If the assumption of normal distribution is violated, transformation or non-parametric testing will be used. Analysis of variance (ANOVA) will be conducted to examine between group differences (separately for the 6- and 12-month assessments), controlling for the effects of baseline characteristics. Repeated-measures mixed models will be used to examine intervention effect (time x intervention), controlling for the effects of baseline characteristics. The analyses will be repeated for absenteeism and presenteeism (secondary objectives).

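### Separate English and French analyses do not estimate whether the effect differs by language; an arm-by-language term with a confidence interval would.

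*Protocol article*

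**What the plan says.** The Limitations section of the Protocol article states: "However, the French materials for the mindfulness relaxation program were not available". It accepts that this could lower effectiveness among French-speaking participants and names the remedy: "We will examine this potential impact by conducting the proposed analyses in English and French speaking participants separately".

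The analyses to be repeated are those in Statistical Analysis. For the primary outcome, "the proportions of MDE over 12 months will be estimated for each group", and these are "compared using chi-square tests between control versus intervention #1, and control versus intervention #2". Logistic regression adjusts for baseline confounders. Changes in the depression and anxiety scores are analysed by t tests, ANOVA and repeated-measures mixed models, and the same is done for absenteeism and presenteeism. The only interaction named is time by intervention. No section gives a language-by-arm term or any other between-language comparison of effects.

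The trial is sized for one whole-arm comparison. The Sample Size Calculation section takes rates from an earlier trial, in which "0.8% and 3.9% of participants in the intervention and control group developed MDE, respectively", and concludes that "374 participants in each arm are needed to detect the difference at a power of 0.80 and alpha level of.05". Recruitment is 400 per arm. The number or share of French speakers is not given.

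**The concern.** The question raised in Limitations concerns a difference: does the intervention work less well in French, where one component is missing? Analysing each language alone answers something else, namely whether an effect can be shown within English speakers and within French speakers. Neither result, nor the pair, comes with an estimate or a standard error for the gap between the two effects.

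The two groups may also differ greatly in size. A smaller French group has less power, so group size alone favours a positive English result beside a null French one. That is the pattern the article already suspects on substantive grounds, so it would be easy to take as confirmation that the missing module cost French speakers some benefit.

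**Working it through.** **Inputs from the Protocol article.** Control rate p1 = 0.039 and intervention rate p2 = 0.008; power 0.80, alpha 0.05; 400 recruited per arm (Sample Size Calculation). Chi-square test of each intervention arm against control (Statistical Analysis).

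**Assumptions, not in the article.** French share 10% to 30%; identical rates in both languages; no dropout in the main case; French speakers spread evenly over the arms.

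**Step 1: reproduce the plan's figure.** Two-sided, pooled variance under the null, no continuity correction, mean rate (0.039 + 0.008)/2 = 0.0235:

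n = [1.96·√(2 × 0.0235 × 0.9765) + 0.842·√(0.039 × 0.961 + 0.008 × 0.992)]² / 0.031² = 373.7, so 374 per arm. This matches.

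**Step 2: power within each language.** Exact binomial enumeration of the uncorrected chi-square test, with E the power in English and F the power in French. As the groups are independent, P(English significant, French not) = E(1 − F), and P(disagreement either way) = E(1 − F) + F(1 − E).

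| French share | Per arm, English/French | E | F | English only | Either way |
|---|---|---|---|---|---|
| 10% | 360/40 | 0.82 | 0.05 | 0.78 | 0.78 |
| 20% | 320/80 | 0.78 | 0.21 | 0.62 | 0.66 |
| 25% | 300/100 | 0.75 | 0.28 | 0.54 | 0.61 |
| 30% | 280/120 | 0.72 | 0.34 | 0.47 | 0.57 |

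Worked line at 20%: 0.783 × (1 − 0.213) = 0.616. Expected French events in that comparison are 80 × 0.039 = 3.1 in control and 80 × 0.008 = 0.6 in the intervention arm.

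**Step 3: sensitivity of the English-only pattern.**
- *Smaller true effect, 20% French.* With a 60% relative reduction (3.9% vs 1.56%) it is about 0.40; with a 40% reduction (3.9% vs 2.34%), about 0.19.
- *20% dropout (320 per arm).* At 10%, 20% and 30% French: 0.734 × (1 − 0.027) = 0.71; 0.674 × (1 − 0.147) = 0.58; 0.604 × (1 − 0.271) = 0.44.

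**Step 4: the interaction test when the effect is identical.** By construction it signals a difference in about 5% of trials. In simulation, a Wald test on the difference in log odds ratios (0.5 added to each cell) signalled in 1.1% to 1.4%; it is conservative because events are few.

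**Step 5: what the interaction can show for MDE.** On the risk-difference scale, with nE and nF per arm and v = 0.039 × 0.961 + 0.008 × 0.992 = 0.0454:
- *Identical effect.* SE = √(v/nE + v/nF). The 95% CI half-width, 1.96 × SE, is 7.0, 5.2 and 4.6 percentage points at 10%, 20% and 30% French, against a planned effect of 3.1 points.
- *Effect wholly absent in French.* The French term becomes 2 × 0.039 × 0.961/nF = 0.0750/nF. The SE is 0.0447, 0.0328 and 0.0281, so 0.031/SE is 0.69, 0.94 and 1.11, and power is about 11%, 16% and 20%.

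**The case against.** The strongest reply is that the article never says significance will be compared across languages. It says the analyses will be run separately, and the planned estimates and regression models would yield language-specific effects, which are worth having. A reader might infer a rule under which an English-only significant result shows lost benefit in French; the text does not state one. This stands, and the probabilities above apply only if the tests are read side by side. It does not repair the gap: separate runs are the only method named, and they produce no estimate of the difference.

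A reader might also infer that the results will usually conflict, or that French speakers will nearly always be non-significant. Neither holds generally. At 30% French the English-only pattern is just under half and French power is 0.34, and the figures fall with a weaker effect. Applying the article's own instrument accuracy (sensitivity 89.6%, specificity 93.9%) to the planning rates gives observed proportions of about 9.4% and 6.8%, and the pattern at 20% French falls to about 20%. The calculation also covers only the MDE chi-square test; the article gives no figures from which to repeat it for the continuous outcomes.

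It can be added that this is one sentence under Limitations in a condensed article, that the primary analysis is untouched, and that the interaction test is itself weak for MDE. All true. The first two limit the weight of the point. The third is a reason to report an interval, not to leave the difference unestimated. That a fuller plan may exist does not change the fact that the article names a method and that it does not match its purpose.

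**Conclusion.** The point holds in limited form. The stated method does not estimate or test the quantity it is meant to examine. If the separate tests are set side by side, an English-only significant result has a chance of about 78% to 47% per comparison under an identical effect. That range rests on the full planning effect, 400 per arm, no dropout and an assumed French share of 10% to 30%. It drops to about 40% or 19% at 20% French if the relative reduction is 60% or 40%. The contrast with about 5% or fewer false signals from an interaction test remains under each of these. The primary comparison is not affected; what is at risk is a conclusion about French speakers that the data could not support.

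**What to change.** Replace the separate-analyses sentence with a single model in all participants containing arm, language and arm-by-language: logistic for MDE, and the planned models for the continuous secondary outcomes. Report the interaction estimate with its 95% CI alongside the language-specific estimates and their CIs, labelled exploratory.

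The cost is a change of analysis wording, with no new data. Two cautions should be written in. For MDE the interaction has low power (about 11% to 20% even if the effect is wholly absent in French speakers) and a wide CI, so a null interaction is not evidence that the missing material had no impact. And language is not randomised, so an interaction could reflect region or other differences between the groups.

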### Conclusion

MDE is a prevalent mental health condition in working men. Because of the stigma against depression and gender/social norms, men who are at high risk of MDE are reluctant to seek help and are lack of skills of self-management. BroHealth is a tool designed to overcome these gaps. The proposed RCT will provide solid evidence about the effectiveness and return on investment of this product.

## Abbreviations

CBT: cognitive behavioral therapy
CIDI: Composite International Diagnostic Interview-Short Form
CIDI-SFMD: Composite International Diagnostic Interview-Short Form for Major Depression
e-mental health: electronic mental health
GAD-7: Generalized Anxiety Disorder
HPQ: Health Performance Questionnaire
ID: identification
LEAPS: Lam Employment Absence and Productivity Scale
MDE: major depression
PHQ-9: Patient Health Questionnaire
PI: principal investigator
RCT: randomized controlled trial
WHO: World Health Organization
